## Abstract

Hormonal changes and physiological alterations in pregnancy increase the susceptibility of the woman to oral diseases such as plaque-induced gingivitis. In individual oral prophylaxis, effective tooth brushing can reduce gingival inflammation. Therefore, it is necessary to update the scientific evidence to identify which type of toothbrush, manual or sonic-powered, is most effective in reducing the incidence of gingivitis in pregnant women. The aim of this clinical trial is to compare the biofilm control effectiveness of two manual and two sonic toothbrushes in pregnant women. This study is designed as a four-arm, parallel, randomized controlled trial with an allocation ratio of 1:1:1:1. The pregnant woman will be included at 15–18 weeks of amenorrhea and followed for 3 months. The primary outcome will be the change in the incidence of gingival bleeding from a baseline and various follow-up periods of the study. Secondary outcomes measures will be to compare clinical effects of the toothbrushes tested on (i) gingival inflammation, (ii) dental plaque, (iii) gingival attachment and (iv) periodontal pocket; and to assess toothbrush acceptability. Thus, identifying the best device for effective tooth brushing in pregnancy could be helpful in reducing and improving the incidence of gingival inflammation.

## 1. Introduction

The World Health Organization visualizes a society where all pregnant women receive quality care during pregnancy, childbirth and postpartum periods [1]. Specifically, antenatal care constitutes a foundation for significant healthcare activities, such as health promotion and diagnosis, as well as disease prevention.

Plaque-induced gingivitis in pregnant women is a common inflammatory periodontal disease that appears from the second or third month of pregnancy with an overall prevalence of 30 to 100% [2,3,4,5,6]. Gingivitis during pregnancy can manifest as swelling, redness, increased volume and gingival sensitivity, but more especially through bleeding, indicating damaged vascularization [7]. Periodontal tissue inflammation as a result of oral biofilm dysbiosis significantly increases during a normal pregnancy, and is exacerbated by elevated levels of characteristic sex steroid hormones [8]. Indeed, inflamed periodontal tissues generate substantial quantities of proinflammatory cytokines, primarily interleukin 1-beta (IL-1β), IL-6, prostaglandin E2 and tumor necrosis factor-alpha (TNF-α), which could potentially exert systemic effects on the woman [9]. Periodontal pathogens, such as *Porphyromonas gingivalis*, can, especially in case of gingival bleeding, penetrate the bloodstream and potentially the placenta, with negative consequences for the pregnancy [10]. The research has affirmed a connection between periodontitis and certain pregnancy complications, including premature birth, low birth weight, intrauterine growth retardation and preeclampsia [11]. 

There is a consensus that adequate control of bacterial plaque, through professional and individual oral prophylaxis, is essential to maintain a symbiotic periodontal microbiota. Therefore, individual oral prophylaxis through standard oral hygiene methods, mainly based on the use of a mechanical toothbrush for the accessible surfaces, has a fundamental role in the prevention of plaque-induced gingivitis [12,13]. And if adequate toothbrushing associated with an effective, acceptable and tissue non-traumatizing toothbrush is the key to disorganizing dental and periodontal biofilms, certain coadjuvant products, such as gels containing natural antioxidant ingredients or others, can contribute to prevent or reduce gingivitis and/or aphthous lesions [14].

Mechanical plaque control involves many processes involving devices such as manual toothbrushes and so-called “intelligent” toothbrushes, which include powered toothbrushes, sonic and ultrasonic toothbrushes, ionic technology toothbrushes, disposable toothbrushes and laser toothbrushes. Continuous progress has been made with the integration of technology to improve the quality of the tools. However, numerous clinical studies have compared plaque removal and other oral health indices with powered and manual toothbrushes, but the results are controversial [15,16,17]. 

New generations of manual toothbrushes mainly based on a high increase in the number of bristles per tooth head would be likely to have optimum effectiveness in disrupting biofilms on accessible surfaces. This increase in the number of bristles is accompanied by a reduction in their diameter, which facilitates access to the gingival sulcus and the flexibility to prevent adverse effects in terms of dental and gingival tissue loss.

Powered toothbrushes, available at a wide range of prices, have been developed to take over the complex movements required of the manual toothbrush and make plaque removal more effective. A variety of powered toothbrushes with different toothbrush head shapes and different types of movement are marketed. Modes of action include counter-oscillation, rotation-oscillation, circular and sonic movements. The most convincing data seem to concern rotation-oscillation brushes, suggesting a more significant reduction in plaque and gingivitis than manual brushes [18,19]. However, sonic toothbrushes seem promising, as their use would be associated with a significantly greater reduction in plaque accumulation and gingival inflammation than toothbrushes with rotating-oscillating heads [20]. In addition, they are claimed to disrupt plaque microorganisms not only at the point where the bristles come into contact with the tooth surface, but also through non-contact energy transfer. The sonic models, called vibratory, vibrate between 15,000 and 30,000 times per minute, and are specifically designed to break up dental plaque through the action of the brush bristles, which vaporize saliva in the form of bubbles. Within sonic technology, different toothbrush head configuration options exist. The analogy with manual toothbrushes is real in terms of assumptions about the effectiveness, trauma and individual acceptability of these different models. The relevance of brush head models is currently debated. 

Furthermore, powered devices address the problem of the wide diversity of recommendations on tooth brushing methods. Similarly, the recent introduction on the market of interactive powered toothbrushes, thanks to the functionalities of applications associated with mobile phones, would provide better results in terms of plaque control and efficient use of brushing time, with better collaboration in patient self-treatment [21]. Interactivity is based on intelligent sensor technology with integrated pressure sensors that provide a warning in the event of brushing excess. Likewise, the brushing process is connected to the company’s application, using software compatible with Android and Bluetooth^®^ 4.0, and via the Bluetooth^®^ wireless application, a personalized progress report is sent back to the user. However, the overall effect size is limited, and the clinical relevance is not yet clear. Studies on the clinical efficacy of sonic brushes have so far been inconclusive.

To deliver on the “WHO Global Strategy for Women’s, Children’s and Adolescents’ Health”, innovative [22], evidence-based strategies for antenatal care are needed. In relation to the prevention and management of gingivitis, questions need to be asked about evidence-based practices during antenatal care that improve outcomes and lead to a positive pregnancy experience. Because of the potential difficulties of disorganizing dental biofilm in pregnant women such as nausea, acid reflux and vomiting, sensitive or bleeding gums, or fatigue [23,24], which can make it more difficult to maintain a regular oral care routine, powered toothbrushes have been advanced as an alternative to manual toothbrushes. In the literature, there are many studies on this topic [25,26,27], but there are currently no significant clinical trials investigating this long-term clinical comparison in pregnant woman. Therefore, the question of whether manual or powered toothbrushes are beneficial for pregnant women remains unresolved. In light of this, there is a need to update new scientific evidence to investigate the effectiveness of different toothbrushing models. Robust clinical research is required to assess their efficacy and acceptability in order to guide professional recommendations. Hence, our research will provide a significant advance in the understanding of the potential of the latest generation of powered toothbrushes to reduce gingival inflammation, and potentially reduce the risk of gingival lesions.

The aim of this randomized controlled clinical trial is, in pregnant women, to compare the efficacy on gingival inflammation of a new generation of connected sonic toothbrush with micro-vibrations, compared with a standard sonic toothbrush and two manual toothbrushes.

## 2. Experimental Design

### 2.1. Trial Design

This clinical study named PRE-IOP (Pregnancy—Individual Oral Prophylaxis) is designed as a four-arm, parallel, randomized controlled trial (ratio 1:1:1:1) (Figure 1). The protocol is presented in accordance with Standard Protocol Items: Recommendations for Interventional Trials (SPIRIT) guidelines [28]. 

### 2.2. Study Setting

The PRE-IOP study will be conducted within the obstetrical department of a private hospital with a level 2B maternity unit, which is the highest level for a private hospital (Majorelle Polyclinic, Elsan group, Nancy, France).

### 2.3. Study Population

#### 2.3.1. Eligibility Criteria

For this clinical study, 120 pregnant women who meet the inclusion criteria will be recruited during their consultation visit with a medical specialist in obstetrics gynecology. During an initial oral examination, a dentist will verify the individual eligibility criteria: (i) female, (ii) 18–40 years old, (iii) pregnant 15–18 weeks amenorrhea, (iv) plaque-induced gingivitis with an intact periodontium or a reduced periodontium, (v) acceptance of study terms and conditions and (vi) signature of informed consent form.

#### 2.3.2. Exclusion Criteria

Exclusion criteria will be (i) women under guardianship; (ii) stage I, II, III periodontitis according to the classification system 2017 [29]; (iii) history or treatment of periodontal disease; (iv) current dental treatment or orthodontic treatment; (v) less than 20 natural teeth, excluding third molars; (vi) taking medication affecting the gum and/or oral mucosa such as anticoagulant therapy, antiplatelet therapy and calcium channel blockers; (vii) use of interdental brushes and/or dental floss and/or mouthwashes; (viii) removable prosthesis; (ix) dental implants; (x) systemic disorder such as hematological disorders, diabetes and risk of infective endocarditis; and (xi) inability to answer questions or non-cooperation.

### 2.4. Materials Description

The materials used in this study are detailed in Table 1. According to manufacturers’ guidelines, sonic toothbrush heads should be replaced every 3 months due to bristle wear. Therefore, new sonic toothbrushes heads will be supplied to participants every 3 months. Similarly, manual toothbrushes will be replaced every 3 months.

### 2.5. Interventions

During the study, the pregnant women will have to brush their teeth twice a day (morning and evening) with the toothbrush corresponding to the arm of randomization assigned (Table 1). All participants will use the same toothpaste 0.243% SnF_2_ (Sensodyne rapid action toothpaste, GSK, London, UK) and they will not be allowed to use complementary techniques (dental floss, interdental brushes, mouthwashes, etc.) during the period of the study. Technical documentation on the use of the devices produced by the manufacturer will be made available to participants. No individual instructions on brushing hygiene techniques will be provided. This trial does not interfere with the organization of care provided during obstetrical visits.

### 2.6. Outcomes

#### 2.6.1. Primary Outcome Measures

Primary outcome will be the change in the incidence of gingival bleeding in pregnant woman (time frame: 3 months).

#### 2.6.2. Secondary Outcome Measures

Secondary outcome measures will compare the effectiveness of the toothbrushes tested on the clinical changes in (i) gingival inflammation, (ii) dental plaque, (iii) gingival attachment and (iv) periodontal pocket (time frame: all outcomes will be measured at baseline (T1), 1 month/T1 (T2) and 3 months/T1 (T3))

Secondary outcomes measures will also be to evaluate (i) oral hygiene attitudes and practices (time frame: baseline (T1)), (ii) attitudes and practices in relation to the toothbrush tested (time frame: 1 month/T1 (T2) and 3 months/T1 (T3)) and (iii) assessment of the acceptability of the toothbrush tested (time frame: 1 month/T1 (T2) and 3 months/T1 (T3)).

### 2.7. Timeline of Participant

The timing of visits will coincide with the usual follow-up visits required for pregnant women. The trial participation schedule is detailed in Table 2.

#### 2.7.1. Pre-Screening and Eligibility Assessment (T0)

Participants will be selected during their gynecologist visit for pregnancy. The obstetrician will present the study to all pregnant women eligible. If pregnant women accept to participate and consent to be screened, an inclusion visit will be scheduled by a dentist. 

#### 2.7.2. Inclusion, Oral Examination and Questionnaire (T1)

Participants will sign the informed consent form. They will have to complete a questionnaire regarding their oral hygiene attitudes and practices (Supplementary File S1) and an oral examination in accordance with clinical practices will be carried out by a dentist who will report the following clinical parameters:(i)Bleeding on probing (BOP): Dichotomous gingival index reporting the presence/absence of bleeding on probing after 30 s (0 = absence of bleeding after 30 s, and 1 = presence bleeding after 30 s). Four sites are recorded per tooth (mesio-buccal, disto-buccal, mesio-palatine and disto-palatine) [30,31].(ii)Gingivitis score (Gingival Index, GI): Measured through visual observation from 0 to 3 (0 = no inflammation; 1 = slight change, slight inflammation in color and little change in texture; 2 = moderate, moderate inflammation, redness, edema and hypertrophy, tendency to bleed on probing; 3 = severe, marked redness, inflammation and hypertrophy; tendency to spontaneous bleeding). Gingivitis score = sum of GI scores divided by number of total sites [32].(iii)Dental plaque score (Rustogi Modified Navy Plaque Index, RMNPI): According to the Navy plaque index modified by Rustogi et al., the presence of plaque deposits is sought on the vestibular and lingual surfaces of the teeth. Each tooth face is divided into 9 areas to which a dichotomous score is assigned (0 = absence of plaque; 1 = presence of plaque). Thus, for each tooth, 18 measurements are carried out. This index makes it possible to detect minimal differences at the partial level of the marginal/interproximal zones, or at the total level of the oral cavity [33].(iv)Probing pocket depth (PPD) score: Measure indicating the distance separating the top of the marginal gingiva from the bottom of the periodontal pocket. The measurement is expressed in millimeters. Four sites are recorded per tooth (mesio-buccal, disto-buccal, mesio-palatine and disto-palatine) [34].(v)Clinical Attachment Loss (CAL) score: Addition of PPD and recession height, which is the distance separating the enamel–cementum junction from the bottom of the pocket. Four sites are recorded per tooth (mesio-buccal, disto-buccal, mesio-palatine and disto-palatine) [31].

PPD and CAL will be assessed following the criteria defined by the consensus report of the 2017 World Workshop on the Classification of Periodontal and Peri-Implant Diseases and Conditions [29], using U.S. Williams PDT sensor probe at a pressure of 20 g (Zila-Pro-Dentec Inc., Batesville, AR, USA). Based on severity-defined stages of interdental CAL and tooth loss, and complexity, extent and distribution, they included a full oral examination of six sites on each permanent tooth. All measures will be performed on all teeth except for third molars. No radiographs will be taken, for ethical reasons.

Four calibrated, properly trained dentists, blinded to group category at the time of the assessment, will perform the periodontal evaluations of all participants. Intraclass correlation coefficients for PPD and CAL will be determined at the level of the site. The intra- and inter-examiner coefficients for CAL will be, respectively, from 0.80 and 0.85, and from 0.75 and 0.85 for probing depth.

#### 2.7.3. Follow-Up Visits (T2 and T3)

Two visits will be made after the inclusion of pregnant woman at T1. Visit T2 will occur one month after T1 and visit T3 will occur three months after T1 (Table 2). At each visit, an oral clinical examination and a questionnaire regarding oral hygiene attitudes and practices in relation to the toothbrush used, specific for each arm of the study (Supplementary Files S2–S5), will be performed. 

### 2.8. Ethics Statement

The PRE-IOP protocol and design were approved by ethical and regulatory authorities, and will be performed in conformity with the Declaration of Helsinki. The Committee for the Protection of Persons Ile de France II (Paris, France) approved the protocol on 3 July 2023. The National Agency for Medical and Health Product Safety registered it on 18 April 2023 (ID-RCB ref: 2022-A02433-40). This study will be conducted in accordance with the methodology of reference MR-001 from National Commission for Information Technology and Liberties (2116544 v 0). This trial was registered with ClinicalTrials.gov, accessed on 7 June 2023 (identification number NCT05945225).

Before taking part in the study, all participants should provide informed consent. The following elements will be included in the consent form: the name and affiliation of principal investigator, a clear description of the purpose of the study, the procedure and the duration of the study, the right to stop at any time, the approval of the ethics committee and a confidentiality guarantee. 

### 2.9. Sample Size

The reduction in gingival bleeding was considered the primary outcome variable and an estimate of a mean difference in reduction was used to calculate the sample size, when the two-sided differences in means between groups (treatment effect) were 5% (estimation extracted from ongoing project in pregnant women in Senegal; unpublished data), with a standard deviation of 10%. Using this estimate with an alpha risk of 5% and statistical power of 90% resulted in the required number of subjects per group of 25. Assuming a potential dropout rate of 20%, 30 participants per group were determined as a target for patient inclusion.

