## 4. Expected Results

The aim of the PRE-IOP randomized controlled trial is to compare the biofilm control effectiveness in pregnant women with four different toothbrushes: two manual toothbrushes and two sonic toothbrushes. The primary endpoint is the evolution in gingival bleeding over the different study periods. In addition to these clinical data, questionnaires on the acceptability of the toothbrushes tested will be analyzed to determine which of the toothbrushes tested is most acceptable to pregnant women. Clinical relevance will allow us to ensure that the outcome of the trial corresponds to a sufficiently large effect on a clinically relevant endpoint. We expect to observe significant differences in the efficiency of the four toothbrushes in disorganizing oral biofilm. One or more of the toothbrushes could prove more effective than the others, which would suggest that the choice of toothbrush has an impact on the reduction in oral biofilm.

These results would support the hypothesis that selecting the appropriate toothbrush, with the adequate brushing technique, can contribute to improving patients’ oral health. Also, these outcomes will provide decision-making support for healthcare professionals involved or not in oral health, to recommend the best devices.

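### The sample size does not follow from its inputs: a 5-point difference with SD 10 needs 85 to 86 women per group for 90% power, and the stated 25 give about 41%

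*Protocol article*

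**What the plan says.** Section 2.9 (Sample Size) takes the reduction in gingival bleeding as the variable for sizing and says that "an estimate of a mean difference in reduction was used to calculate the sample size". The inputs are all printed:

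- effect: the "two-sided differences in means between groups (treatment effect) were 5" per cent, taken from unpublished data of an ongoing project in Senegal;
- spread: "with a standard deviation of 10" per cent;
- error rates: "alpha risk of 5" per cent and "statistical power of 90" per cent.

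The section then states that this estimate with an "alpha risk of 5% and statistical power of 90% resulted in the required number of subjects per group of 25", and raises the 25 to 30 per group for 20% dropout. Sections 2.3.1, 3.1 and 3.2.1 carry the figure forward as 120 women, and section 2.1 confirms four parallel arms at 1:1:1:1. Section 2.9 mentions no baseline adjustment, repeated-measures gain, pooling of arms or multi-group contrast.

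**The concern.** A difference of half a standard deviation is a moderate effect, and 25 per group is far too few to detect it with 90% power in a two-group comparison. This is not a detail left to a fuller document: the inputs and the answer stand side by side and do not agree.

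Section 2.9 is the only justification given for the size of the trial. If the printed effect and SD are right, a pairwise comparison would miss the difference that the protocol calls its treatment effect more often than it would detect it. A non-significant result could then be taken as evidence that the brushes perform alike, when the trial could not separate a 5-point difference from none. Section 4 intends the results to support recommendations of devices by health professionals, so readers need to know how much a null result can tell them.

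**Working it through.** **Inputs (section 2.9).** Difference δ = 5 points, SD σ = 10 points, two-sided α = 0.05, power 0.90, equal groups. The standardised difference is d = 5/10 = 0.5.

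**Attempt to reproduce 25.** For two independent means:

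n per group = 2 × (z₀.₉₇₅ + z₀.₉₀)² × (σ/δ)² = 2 × (1.960 + 1.282)² × (10/5)² ≈ 84.1, so 85.

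The exact t-test solution is 85.03, so 86. Over four arms that is 340 to 344 evaluable women, against 100 (4 × 25) in the protocol.

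**Power at the planned size** (noncentral t, d = 0.5, two-sided 5%):

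| Evaluable per group | Power for 5 points |
|---|---|
| 24 (30 less 20%) | 39.6% |
| 25 | 41.0% (42.4% by normal approximation) |
| 30 (no dropout) | 47.8% |

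**What 25 per group can detect.** The t-test reaches 90% power at d = 0.936, which is 9.4 points at SD 10, or 5 points at SD 5/0.936 = 5.3. It reaches 80% power at d = 0.809, which is 8.1 points.

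**Precision.** The standard error of a pairwise difference is 10 × √(2/25) = 2.83 points. The 95% confidence interval is then about ± 2.01 × 2.83 = ± 5.7 points, wider on each side than the target difference.

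**Other readings, with δ = 5 and SD = 10:**

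| Reading | Needed per group for the stated power | Power at 25 per group |
|---|---|---|
| One-sided, 90% | 70 | 54% |
| Two-sided, 80% | 64 | 41% |
| One-sample or paired, two-sided, 90% | 44 | 67% |
| SD divided by √2, two-sided, 90% | 43 | – |
| Two sonic arms against two manual arms, pooled, 90% | 43 | 70% (50 v 50) |
| One arm against the other three pooled, 90% | 57 in the single arm | 57% (25 v 75) |
| Four-group F-test, largest difference 5 points, 90% | 58 to 115 | 27% to 52% |

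The F-test range depends on the pattern of the four means: two extremes 5 apart with the others midway (f = 0.177), 27%; one arm differing (f = 0.217), 40%; two arms against two (f = 0.25), 52%.

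One formula does land on 25: one-sample, one-sided, 80% power, (1.645 + 0.842)² × (10/5)² ≈ 24.7. It contradicts three printed inputs: two-sided, between groups, and 90%.

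**Multiplicity (assumption, since the article names no procedure).** With Tukey adjustment over the six pairs, power per pair at 25 per group is about 20%. With Bonferroni it is about 18%, and 90% power would need about 125 per group.

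**Dropout step.** The 30 equals 25 × 1.2. To keep 25 after losing 20% needs 25/0.8 = 31.25, so 32. This is a small matter beside the main error.

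**The case against.** The strongest counter-argument is that 41% belongs to a change-score t-test between two arms, while section 3.3.3 plans a linear mixed model on repeated, log-transformed bleeding measurements with covariates, which could be more powerful. As an illustration, take SD 10 as the single-visit SD, two arms against two (f = 0.25), and a between-group F-test on repeated measurements, with noncentrality f² × N × m / (1 + (m − 1)ρ) and N = 100. With m = 4 measurements and within-subject correlation ρ = 0.2 the noncentrality is 15.6 and power about 92%; with ρ = 0.5 it is 74%.

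This does not rescue section 2.9. The section describes a difference in mean reduction and gives neither a correlation nor a repeated-measures model. Table 2 schedules three bleeding assessments, not four, and with m = 3 and ρ = 0.2 power is about 87%. The illustration also counts baseline as if the arms already differed there; with the two follow-up visits only (m = 2, ρ = 0.2) power is 76%. Baseline adjustment alone would need a baseline–outcome correlation of about 0.85, with 10 as the unadjusted SD.

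Three limits do stand. First, the statement that the difference would more often be missed than found applies to a pairwise comparison; the pooled contrasts have 57% and 70% power, still well short of 90%. Second, the source data are unpublished, so the article cannot show whether the sample size or a printed input is wrong. Third, section 4 says "We expect to observe significant differences in the efficiency of the four toothbrushes in disorganizing oral biofilm", but that concerns biofilm, for which no effect or SD is given. The power figures here concern bleeding and do not bear on that sentence.

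**Conclusion.** The concern holds: section 2.9 is wrong as written. On its own inputs the requirement is 85 to 86 evaluable women per group, about 3.4 times the stated 25. Pairwise power at 25 is 41%, which is 49 percentage points below the claim. These figures assume a two-sample comparison of mean reductions, a common SD of 10 points, two-sided 5% per comparison and no multiplicity adjustment; adjustment would lower the power further. None of the alternatives compatible with the printed description reaches 90% at 25 per group. If an SD near 5.3 or a difference near 9.4 points was in fact used, the sample size may be sound and the printed input is the error. Either way the text needs correcting.

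**What to change.** First reconcile the inputs with the sample size by going back to the unpublished source data and the original calculation.

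- If a different SD, effect or model was used, print it in section 2.9 with its source, together with any correlation the calculation relies on.
- If 5 and 10 points are confirmed and recruitment stays at 120, replace the power statement with text such as:

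> With 25 evaluable women per group, an SD of 10 points and a two-sided alpha of 5%, power for a 5-point difference between two arms is about 41%. The difference detectable with 90% power is about 9.4 points (8.1 points with 80% power). A non-significant pairwise result is inconclusive and will be reported with its confidence interval.

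- If 90% power for 5 points is to be kept, the trial needs 85 to 86 evaluable per group. At 20% dropout that is 85/0.8 to 86/0.8, so 107 to 108 enrolled per group, or 428 to 432 women in four arms.

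The first two options change wording only and need no extra participants; their cost is a less favourable or differently justified power statement. The third is a different trial in size and is set out for completeness.

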## 3. Procedure

### 3.1. Recruitment

The PRE-IOP study will recruit 120 pregnant female volunteers. The obstetrician will propose the study to all women between 15 and 18 weeks of amenorrhea and between 18 and 40 years of age. If the pregnant woman accepts to be included in the study, then the obstetrician will give her a trial information sheet and a consent form, and an inclusion visit will be planned with a dentist. The total number of pregnant women screened and recruited will be referenced. Participants will not receive any financial compensation.

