### 3.2. Allocation of Interventions

#### 3.2.1. Allocation

In the PRE-IOP trial, participants will be randomly assigned at the start of the trial to one of four arms: Arm 1—Interactive sonic toothbrush, DiamondClean 9000 Sonicare (Philips^®^, Suresnes, France); Arm 2—Non-interactive sonic toothbrush, HydroSonic Easy (Curaden^®^, Kriens, Switzerland); Arm 3—Manual toothbrush, Oral-B 123 (Procter & Gamble^®^, Asnières-sur-Seine, France); and Arm 4—Manual toothbrush Curaprox CS 5460 (Curaden^®^, Kriens, Switzerland)) (Table 1). Random arm allocation will be computer-generated by the study manager using e-CRF Voozalyon 1.3 (Voozanoo, Caluire, France). Participants will remain in the same arm during the study period. Eligible pregnant women will be included in the study and numbered according to the inclusion order up to the number of subjects (*n* = 120, 30 pregnant women per group).

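### Minor: 30 per group does not keep the stated 25 after 20% dropout; it leaves an expected 24, and keeps 25 only if dropout is at most 16.7%

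*Protocol article*

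**What the plan says.** Section 2.9 (Sample Size) of the protocol article assumes a between-group difference in means of 5%, an SD of 10%, a two-sided comparison, an alpha of 5% and 90% power. It says that this "resulted in the required number of subjects per group of 25". The next sentence adds the allowance for loss: "Assuming a potential dropout rate of 20%, 30 participants per group were determined as a target for patient inclusion".

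The target is then carried through the article. Section 3.1 (Recruitment) says "The PRE-IOP study will recruit 120 pregnant female volunteers", and section 3.2.1 (Allocation) numbers women in order of inclusion up to 120, with "30 pregnant women per group". Those two places only repeat the target and contain no separate error. The article does not write out the inflation formula, and it describes no replacement of women who drop out.

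**The concern.** A dropout allowance is meant to ensure that the required number is still there after the assumed loss. Here the required number, the loss and the target are all printed, and they do not agree: 20% off the target ends below the required number. The usual cause is to multiply by (1 + d) where one should divide by (1 - d), with d the dropout rate. The two are close when d is small, but they differ visibly at 20%.

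What is at stake is a stated property of the design. A reader takes from section 2.9 that the trial can lose a fifth of its participants and still have the number it calls required. On its own figures it can lose only a sixth. The step also matters for any revision, because the same method applied to a larger base number gives a larger shortfall.

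**Working it through.** **Inputs, all from section 2.9:** required n = 25 per group; dropout d = 0.20; target 30 per group; difference 5, SD 10 (standardised difference 0.5), two-sided alpha 0.05, power 0.90. Section 2.1 gives four arms at 1:1:1:1.

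**1. Reproducing the stated target.**
- n x (1 + d) = 25 x 1.2 = 30, and 30 x 4 = 120. Both match exactly.
- n/(1 - d) = 25/0.8 = 31.25, rounded up to 32; 32 x 4 = 128. This does not match.

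**2. What 30 delivers at the stated dropout.**
- 30 x (1 - 0.20) = 24 per group; 24 x 4 = 96, against 25 x 4 = 100.
- Largest dropout that still keeps 25: 1 - 25/30 = 5/30 = 16.7%.
- Check on 32: 32 x 0.8 = 25.6, which keeps at least 25.

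**3. Effect of this step on power.**
- Taking the plan's premise that 25 per group gives 90% (two-sample t-test, two-sided 5%): the standardised difference that does so is 0.936, and at 24 per group it gives 88.7%. The normal approximation gives 88.8%. The loss is about 1.3 points.
- Using the printed inputs (standardised difference 0.5): 41.0% at 25 and 39.6% at 24. The loss is 1.4 points.

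**4. Separating this from the base number.** With the printed inputs, n = 2 x (1.960 + 1.282)^2 / 0.5^2 = 84.06, so 85 per group before dropout by the normal approximation. The t-test gives 89.99% power at 85 and 90.3% at 86. The gap between about 40% and 90% power therefore comes from the 25, not from the dropout step.

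**5. What the method would do to a larger base.** For 85 per group, 85 x 1.2 = 102, while 85/0.8 = 106.25, so 107. The difference is 5 per group, or 20 women over four arms.

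**6. Whether every arm would fall short.** As an illustration, assume that each of 30 women drops out independently with probability 0.20 (an assumption, not in the article). The chance that a given arm ends with fewer than 25 is then about 57%. At least one of four arms does so with probability about 97%, but all four do so with probability only 0.572^4, about 11%.

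**The case against.** The strongest case on the other side concerns weight, since the arithmetic is not in doubt.

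- **The shortfall is tiny.** One woman per group and little more than one power point would change no decision about the trial. This stands, and it is why the point is minor.
- **The 25 is itself not supported by the inputs.** Protecting exactly 25 protects little, and the sentence must be rewritten anyway once the base number is corrected. This also stands. A reader might infer that 32 per group, 128 in total, would repair the sample size. It would not: 32 is right only conditional on 25.
- **The mechanism is inferred.** A reader might take it as established that the authors multiplied by 1.2. The article shows only inputs and result; the match is exact, but rounding to a convenient 30 is also possible. The inconsistency does not depend on which it was, because 30 x 0.8 = 24 either way.
- **Twenty-four is an expectation.** A reader might infer that every group will fall below 25. The 20% is called a potential rate and losses will differ between arms, so the documents do not support that. Section 3.3.3 also plans a linear mixed model with repeated bleeding measurements, so a woman seen at one month and lost before three months can still contribute. This softens the consequence but does not remove the mismatch, because the primary time frame in section 2.6.1 is three months.
- **Dropout might be meant as a fraction of completers.** Under that reading 30 would be right. But section 2.9 attaches the rate to a target for inclusion, so the natural denominator is the women included.

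**Conclusion.** The point holds as a minor arithmetic error, secondary to the base sample-size error in the same section. At the stated 20% dropout, 30 per group leaves an expected 24 rather than the required 25 (96 rather than 100 in total), and the true tolerance is 16.7%. The cost of this step alone is one participant per group and 1.3 to 1.4 power points.

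This rests on three assumptions: dropout is counted among the women included, it is equal across arms on average, and those who drop out are not replaced. The article describes no replacement, and section 3.2.1 stops inclusion at 30 per group. The power figures assume a two-sided two-sample t-test between two arms without adjustment for multiple comparisons.

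A reader who sees 39.6% might attribute the low power to the dropout allowance. That would be wrong: power on the printed inputs is already 41.0% at 25 per group.

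**What to change.** Keep 120 and restate the one sentence in section 2.9 in either of two ways: 30 per group allows for 16.7% dropout while retaining 25, or 20% dropout leaves an expected 24 evaluable women per group. Sections 3.1 and 3.2.1 then need no change, and neither recruitment nor analysis is affected. The cost is a rewording.

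Two conditions go with it. Any recalculated sample size should be inflated as n/(1 - d), rounded up. The stated 90% power should be corrected together with the base number and not in this sentence: power at 24 on the printed inputs is about 40%, so quoting it beside an uncorrected 90% would put a contradiction into the same paragraph. That larger correction is not a one-sentence change, and its cost does not belong to this point.
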